##### Mediators

###### Overview

The analysis of the mediators of the experimental conditions can be roughly subdivided into two steps: first analyze the primary factors individually for their longitudinal correlations with the outcome (Step 6), then combine the relevant factors in a multivariate analysis (Step 7). The specific hypothesis on the mediating factors of the interventions in this study are shown in Textbox 2.

###### Step 6

For analyzing the mediators of the experimental conditions, first we want to see whether there is a correlation between the growth trajectories of our outcome parameter and the potential mediator over time. The hypotheses considering mediators are shown in Textbox 2. The combined data from the participants in the first semester and data from the preferentially assigned participants in the second semester will be used.

The following subhypotheses will be tested for each primary mediator (these are also shown in Figure 5):

Is the growth of the primary outcome (Sy) for the entire study population correlated with growth of the potential mediator (Sz)?Is such correlation independent of group?Does the potential mediator change over time in the specific group, so is the slope factor (Sz) substantially unequal to zero?Is the slope factor in the specific group substantially greater than the slope factors in the other groups?

In these 4 subhypotheses, the first is congruent with testing the “conceptual theory” in classical mediation analysis, and subhypothesis 3 with testing the “action theory.” If subhypotheses 1-4 all are true, the factor will be considered a specific mediator for that intervention. If subhypotheses 1, 2, and 3—but not 4—are true, the factor will be considered a general mediator for fatigue severity. If either subhypothesis 1 (conceptual theory) or 3 (action theory) is false, the factor will not be considered a mediator.

Hypotheses on mediators.We expect that, for AAF, increasing mean cumulative daily physical activity and reductions of daily physical activity decline are specific mediators.We expect that, for eMBCT, developing mindfulness skills is a specific mediator.We expect that sleep quality, working alliance, sense of control over fatigue, credibility, and expectancy are generic mediators for both e-therapies.The mediating role of the following factors will be explored: number of sessions completed, changes in causal attributions [99], decreased catastrophizing thoughts about fatigue [8], decreased fear of cancer recurrence [100,101], changes in perceived activity [102], increased self-efficacy on physical activity [103].

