## Methods

### Design

A randomized controlled trial is performed including 3 parallel conditions: 2 experimental conditions (AAF and eMBCT) and a minimal intervention control condition. The intervention period is 9 weeks for all 3 conditions. Both experimental conditions are made as similar as possible in terms of time-investment and contact intensity with the therapist. Outcomes are self-reported and are Web-assessed at baseline (T0), 2 weeks post-intervention (T1), and at 6 months (T2) and 12 months (T3) after baseline. Figure 3 shows a schematic summary of the trial design.

The baseline assessment consists of 3 time-points: (1) T0a, the assessment to check eligibility; (2) T0b, the main baseline assessment taken after the eligibility check and informed consent, but naive of condition; and (3) T0c, directly after randomization for assessing the participant’s credibility and expectancy about the condition. All participants are invited to fill out short questionnaires in weeks 1, 2, 3, 4, 6, and 9 (Mi) of the intervention period in order to study mediation of the interventions.

After T2, patients in the control condition are offered 1 of the 2 experimental interventions, again in a research setting. Please note that the first 4 participants of this trial were randomized to 1 of the experimental conditions for the second semester, but to minimize dropout, all other patients will be allocated based on their own preference. During this second intervention period, these participants will again be assessed in weeks 1, 2, 3, 4, 6, and 9 (Mi’), the second week after the intervention (T1’), and 6 months after the second allocation (T2’). Participants in the control condition that are preferentially allocated to eMBCT after T2 do not wear the accelerometer during the second semester.

The protocol allows delay within the intervention period of a maximum of 2 weeks in case of, for example, illness or holiday. For all participants, the duration of their participation is approximately 12 months. Additional qualitative feedback will be obtained through explorative interviews with a subset of participants in the experimental condition shortly after T1 or T1’.

This trial was approved by the Twente Medical Ethical Committee (Enschede, the Netherlands) under number P12-26 and has been registered at The Netherlands National Trial Register under number NTR3483 [42].

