	Self-efficacy on activities	Selected items from the self-efficacy scales of Bandura [71] and Rodgers [72,73]: 13 items on a 0-100 NRS; subscales: planning and coping.	b		x		
	Catastrophizing	Fatigue Catastrophizing Scale [74,75] 9 selected items on a 5-point Likert scale.	b		x		
	Fear of cancer recurrence	Two selected items on a 7-point Likert scale [76].	b		x		
	Causal attributions	One self-conceptualized open answer question that translates to: “What do you consider as the cause of your fatigue?”	b		x		

^a^Baseline assessment T0 consists of 3 time-points: T0a: before eligibility check, T0b: after inclusion, and T0c: after randomization. T0c’ is assessed after preferential allocation.

^b^Mi and Mi’ = assessments at week (i=) 1, 2, 3, 4, 6, 9 of the intervention

^c^All physical activity measurements are blind except for the experimental activity feedback condition at M3, M6, and M9. In the second semester, M3’, M6’, and M9’ do not include a physical activity measurement in the mindfulness condition.

**Table 3 table3:** Other assessments.

Demographics, medical history, and control factors	T0^a^	T1/T1’	T2/T2’	T3
Age, gender, education, family status, nationality, time since diagnosis, time since previous treatment, fatigue duration, psychological counseling in the past, comorbidity.	a			
Cancer type, cancer treatment, perceived life threat of cancer (7-point Likert scale), known heredity of cancer (yes/no/don’t know), former experience with attention focusing exercise (yes/no), religious beliefs, perceived social support (Multidimensional Scale of Perceived Social Support [77]: 12 items on a 7-point Likert scale).	b			
Medication use, substance use (caffeine, nicotine, alcohol, drugs), quality of life (1 item on a 0-10 NRS).	a	x	x	x
Pain intensity and limitations by pain (2 items on a 7-point Likert scale), body mass index.	b	x	x	x
Life events since previous assessment, professional help received for fatigue outside the scope of the study protocol.		x	x	x
Perceived effectiveness of the intervention (5 items of which 1 item 0-10 NRS and 2 yes/no questions), perceived social support in following the intervention (1-10 NRS).		x		
Social desirability: 6 selected items from the Balanced Inventory of Desirable Responding [78] on 5-point Likert scale.			x	

^a^Baseline assessment T0 consists of 3 time-points: T0a: before eligibility check; T0b: after inclusion; and T0c: after randomization.

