**Figure 5 figure5:**
[figure not shown]
Simplified representation of a correlated growth model in which Iy and Sy represent the intercept and slope factors of the latent growth model of the outcome parameter, and Iz and Sz represent the latent growth factors of the mediator. H1-4 represent the 4 subhypotheses of Step 6. All indicators have been left out for clarity.

###### Step 7

The next step in studying potential working mechanisms is a single-step, multiple-mediation analysis using structural equation modeling [104-106]. By estimating such a model, we expect to obtain a comprehensive model for all the working mechanisms of the intervention. It should be noted that this model assumes that an intervention works in the same way for all participants in a particular group [107]. Again, data from both semesters will be used.

A separate model will be tested for each intervention. Each model will have the following paths (Figure 6), where X=independent variable (1/0 for specific intervention vs control group), Y=outcome variable (difference score T2-T0b of the primary outcome measure), and Z=mediator:

a: X regressed on Z.b: Z regressed on Y;c’: direct effect of X on Y.

For each experimental intervention, the starting model will consist of all the significant primary mediators of Step 6 that have also been assessed in the control group. In other words, the factors that have shown to be mediators in the correlated growth model will be the starting point for this model. The models will then be complemented with the secondary mediating factors described in Textbox 2. Mediating factors for which the indirect effect (a × b) is insignificant will be removed stepwise, after which a final model will be created.

Model fit, standardized path coefficients—including indirect effects—and the total effect of at least the first and final models will be reported with 95% confidence intervals.

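### Mediation Steps 6 and 7 pool randomized first-semester records with self-selected second-semester records from former controls, so the between-group mediation estimates lose their randomized basis

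*Protocol article*

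**What the plan says.** Step 6 (Mediators) defines its data set as follows: "The combined data from the participants in the first semester and data from the preferentially assigned participants in the second semester will be used". Step 7 adds: "Again, data from both semesters will be used". Step 7 fits one model per intervention, with "X=independent variable (1/0 for specific intervention vs control group), Y=outcome variable (difference score T2-T0b of the primary outcome measure), and Z=mediator".

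The second-semester participants are described under Methods, Design: "After T2, patients in the control condition are offered 1 of the 2 experimental interventions, again in a research setting". The first 4 were randomized between the two interventions, but "to minimize dropout, all other patients will be allocated based on their own preference". Credibility and expectancy, which Textbox 2 lists as expected generic mediators, have their second-semester starting value at T0c', which according to the footnote to Table 2 "is assessed after preferential allocation".

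For effectiveness, by contrast, Step 1 and the Figure 3 caption restrict the data to the first semester. The Power Analyses section counts 110 completers per experimental intervention over both semesters, and 198 after exclusions.

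**The concern.** A control who crosses over and completes contributes an X=0 record from the first semester and an X=1 record from the second. The X=1 record differs from a randomized one in three ways. The person chose the intervention. The person has already had the psycho-educational e-mails, whose content is also part of both interventions. And no untreated group runs alongside, because every control is offered treatment after T2.

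The X=1 versus X=0 comparison then mixes the intervention effect with preference, prior exposure and period. This reaches the Step 7 a path and total effect, and Step 6 subhypothesis 4, which compares slopes between groups and decides whether a mediator is called specific or general. Separating specific from nonspecific mechanisms is the reason the article gives for having three randomized arms.

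Two definitions add to the problem. The outcome is given only as "Y=outcome variable (difference score T2-T0b of the primary outcome measure", which for a crossing control is the change over the control period. And five mediators (physical activity, activity self-efficacy, catastrophizing, fear of recurrence, causal attributions) are not measured at T2, so their latest value before second-semester treatment is from T1.

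**Working it through.** **1. Reproducing the planning figures (Power Analyses).** Assume 330 split equally, 110 per arm.
- Experimental arms at T2: 110 × 0.70 = 77 each.
- Controls at T2: 110 × 0.85 = 93.5, stated as 94.
- Second-semester completers: 94 × 0.70 = 65.8, about 66. An even split (assumed) gives 33 per intervention.
- Per intervention: 77 + 33 = 110, as stated. After the 10% exclusion: 220 × 0.90 = 198, as stated.

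The stated 110 and 198 are reached only by counting crossed-over controls as treated. Their share is 33/110 = 30%. In any one Step 7 model, 33/94 = 35% of the controls appear twice.

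**2. Shift in the Step 7 contrast.** Let μ be the expected change in randomized treated participants and μ + d that in second-semester participants, with second-semester Y taken as T2' − T2. The pooled X=1 mean is (77μ + 33(μ + d))/110 = μ + 0.3d.

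The documents give no value for d, so a range of 0.1 to 0.5 SD is assumed. The naive SE in SD units is √(1/110 + 1/94) = 0.140.

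| d (SD) | shift 0.3d (SD) | rejection rate of a nominal 5% test, no true effect |
|---|---|---|
| 0.1 | 0.03 | 5.5% |
| 0.2 | 0.06 | 7.1% |
| 0.3 | 0.09 | 9.8% |
| 0.5 | 0.15 | 18.7% |

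**3. Two records from one person.** No person-level term is described. If the records were treated as independent, the true variance would be 1/110 + 1/94 − 2r × 33/(110 × 94), where r is the correlation between a person's two change scores (assumed).
- r = −0.5: 0.01973 + 0.00319 = 0.02292; SE ratio true/naive 1.08; type I error 6.9%.
- r = 0: 5.0%.
- r = +0.5: 0.01973 − 0.00319 = 0.01654; SE ratio 0.92; type I error 3.2%.

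A negative r is plausible if T2 both ends the control period and starts the second semester, but the sign is not established.

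**4. Outcome taken literally.** With Y = T2 − T0b for everyone, a crossing control would carry the same control-period change in both records. If the crossing controls have the average control change, the contrast shrinks to 77/110 = 0.7 of its value. T2' − T2 is presumably meant, but it is not stated.

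**5. Price of using first-semester data only.** The article's criterion is f² = .08, alpha = .05/6, power .80, about 254 needed. A noncentral F test with 6 numerator df and noncentrality f² × N needs N = 252, close to the stated figure. First-semester experimental completers after exclusions: 154 × 0.90 = 138.6, about 139.

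| N | power, 6-df test | power, 1-df test |
|---|---|---|
| 254 | 0.81 | 0.97 |
| 198 | 0.64 | 0.90 |
| 139 | 0.41 | 0.74 |

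Each Step 7 model goes from 110 vs 94 to 77 vs 94. The SE of the contrast rises from 0.140 to √(1/77 + 1/94) = 0.154.

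**The case against.** The pooling is disclosed, serves a secondary objective, and is what brings the numbers to 198 against the 254 required. A clustering term is a detail that an article may leave to a fuller plan. Subhypotheses 1 to 3 of Step 6 concern correlated growth and within-group slopes and are not randomized contrasts. The mediator-to-outcome path is unrandomized in any design. All of this stands, and it limits the point to the a path, the total effect and subhypothesis 4. It does not remove the point, because the article itself fixes the pooling, and a clustering term would not cure self-selection or the missing concurrent control.

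A reader might infer more than the documents support:
- *Every control is used twice.* No: about 33 of 94 in any one Step 7 model. Controls lost before T2 or during the second semester do not supply a completed second record.
- *Five mediators have no pre-treatment value in the second semester.* Table 2 schedules them at T0b and T1, both before that treatment. The values are older, not absent.
- *The records are analysed as independent and the confidence intervals are too narrow.* The text is silent on dependence, and the direction of any error turns on an assumed correlation.
- *The change score biases the result.* In randomized data it does not bias the total effect. It costs precision and leaves baseline fatigue uncontrolled in the mediator-to-outcome path.

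**Conclusion.** The concern holds for the mediation objective. As written, Steps 6 and 7 produce a between-group comparison labelled intervention versus control in which about 30% of the treated records are self-selected, previously exposed former controls with no concurrent comparison group. The size depends on d, which the documents do not give. The 30% share rests on the planning attrition rates, equal arms and an even split of preferences.

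The effect of repeated use of the same people is modest and of unknown sign; self-selection and the missing concurrent control are the main defect. It is unclear whether the 4 participants randomized in the second semester enter: Step 6 names only the preferentially assigned, Step 7 both semesters. The primary effectiveness analysis uses first-semester data only and is untouched.

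**What to change.** 1. Make the first-semester randomized data the main basis for the Step 7 a path and total effect and for Step 6 subhypothesis 4.
2. Report the pooled analysis as supportive, with participant as cluster, a semester/preference indicator, and second-semester Y defined from T2 to T2'. Say how the 4 randomized second-semester participants are handled, and that T1 is the latest pre-treatment value for the five mediators not measured at T2. Since all second-semester records have X=1, once semester is in the model they add essentially nothing to the X contrast; they mainly inform the mediator-to-outcome path.
3. In Step 7, adjust for T0b fatigue, and for the baseline mediator where one exists, instead of using an unadjusted change score. With equal variances and correlation ρ between T0b and T2, the variance relative to a change score is (1 − ρ²)/(2(1 − ρ)) = (1 + ρ)/2, that is 0.65 to 0.75 for an assumed ρ of 0.3 to 0.5. This gains precision for the total effect; it does not correct a bias in it.

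The changes are to wording and need no new data. The cost is sample size: 77 vs 94 in place of 110 vs 94 per model, and about 139 in place of 198 experimental completers, with power on the 6-df criterion falling from about 0.64 to 0.41. The plan should state this loss. How far baseline adjustment would repay it for the indirect effects has not been calculated.

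### Step 6 words the mediator–fatigue link as a correlation over all arms together, so a factor that treatment shifts alongside fatigue can be labelled a mediator without any link to fatigue within arms

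*Protocol article*

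**What the plan says.** The Mediators section of the protocol article sets four subhypotheses in Step 6 for each primary mediator.

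- Subhypothesis 1, described as the test of the conceptual theory: "Is the growth of the primary outcome (Sy) for the entire study population correlated with growth of the potential mediator (Sz"?
- Subhypothesis 2: "Is such correlation independent of group"?
- Subhypothesis 3, described as the action theory: "Does the potential mediator change over time in the specific group, so is the slope factor (Sz) substantially unequal to zero"?
- Subhypothesis 4 asks whether the mediator slope in that group exceeds the slopes in the other groups.

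The decision rules follow directly. "If subhypotheses 1-4 all are true, the factor will be considered a specific mediator for that intervention". If 1, 2 and 3 hold but 4 does not, "the factor will be considered a general mediator for fatigue severity". Exclusion is narrower: "If either subhypothesis 1 (conceptual theory) or 3 (action theory) is false, the factor will not be considered a mediator".

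On the data: "The combined data from the participants in the first semester and data from the preferentially assigned participants in the second semester will be used". Step 6 also acts as a screen, since in Step 7 "the starting model will consist of all the significant primary mediators of Step 6 that have also been assessed in the control group". Step 7 then models the outcome with the mediator path b and a direct effect of the intervention X side by side, and removes factors whose indirect effect is not significant.

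**The concern.** The conceptual theory says that patients whose mediator changes more also change more in fatigue. A correlation over the whole study population answers a different question. It combines the relation inside each arm with the covariance of the arm means. If an intervention moves the factor and also moves fatigue by some other route, the second part alone makes the overall correlation non-zero. Subhypothesis 1 then partly repeats the treatment effect and the action theory, and is no longer a separate test.

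Subhypothesis 2 is the only other condition on this link. If it means that the correlation is the same in each arm, correlations of zero in all three arms satisfy it. Subhypotheses 3 and 4 concern only whether the factor moved. A by-product of treatment could therefore meet the Step 6 rule and be called a specific or general mediator. Identifying mediators is the trial's second objective.

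**Working it through.** **Inputs from the article.** The power section expects 330 participants, so 110 per arm, with attrition of 30% in the experimental arms and 15% in the control arm: 110 × 0.70 = 77 and 110 × 0.85 = 93.5, rounded to 94. This reproduces the plan's own 77/77/94, a total of 248. Frequentist significance is at .05. The plan gives no operating figure for Step 6.

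**Assumptions not in the article.** The within-arm correlation of Sy and Sz is zero. Slopes are treated as observed, normal, with unit SD within arm. The arm shifts d are in within-arm SD of slope. Signs are ignored, since a falling fatigue slope only reverses the sign of the correlation.

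**Expected overall correlation, both experimental arms shifting both variables by d.** Let p be the share in the experimental arms: p = 154/248 = 0.621 and p(1 − p) = 0.2354. Then

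r = 0.2354 d² / (1 + 0.2354 d²).

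The Fisher-z approximation has signal u = atanh(r) × √(248 − 3) = atanh(r) × 15.65. The pass rate is Φ(u − 1.96) + Φ(−u − 1.96).

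| d | r | u | pass rate, formula | pass rate, simulation | simulation, subhypothesis 2 (equal correlations) also passed |
|---|---|---|---|---|---|
| 0.3 | 0.021 | 0.32 | 6% | 6% | 6% |
| 0.5 | 0.056 | 0.87 | 14% | 14% | 13% |
| 0.8 | 0.131 | 2.06 | 54% | 54% | 52% |
| 1.0 | 0.191 | 3.02 | 86% | 87% | 83% |

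The simulation used 10,000 trials per row. Separate runs gave 54–56% at 0.8 SD, hence about 55%. With 110/110/94 records, a rough allowance for second-semester data, the rates are nearly the same: 14%, 55% and 88% at 0.5, 0.8 and 1.0 SD.

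**Factor moved in one arm only.** Textbox 1 expects fatigue to fall in both experimental arms. Take a factor moved 1.0 SD in one arm (share 77/248 = 0.3105) and fatigue moved 0.8 SD in both:

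- covariance = 1.0 × 0.8 × 0.3105 × (1 − 0.621) = 0.094
- variance of Sz = 1 + 0.3105 × 0.6895 = 1.214
- variance of Sy = 1 + 0.64 × 0.2354 = 1.151
- r = 0.094 / √(1.214 × 1.151) = 0.080

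The simulated pass rate is 23% (22% with subhypothesis 2). With both shifts at 0.8 SD it is about 18%, and at 0.5 SD about 7%.

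**Arm means removed.** With the correlation taken after centring each arm, the pass rate is about 5% in every setting above.

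**Step 7.** I added to subhypotheses 1 and 2 the requirement that both a and b be significant in the comparison of one intervention with control, with b adjusted for X. An unrelated factor then survives in 1–3% of trials in every setting, including 1.0 SD.

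**The case against.** Four objections carry weight.

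*The text may intend a within-arm parameter.* Step 1 uses a multiple-group growth model, and subhypotheses 3 and 4 need group-specific slopes. In such a model the Sy–Sz covariance is within arm and the problem disappears. Subhypothesis 2 could also mean that the correlation persists once group is accounted for. The joint false pass rate is then at most about 6%. Figure 5, which places the four subhypotheses in the model, is not available here. This stands as a possible reading. The written rule nevertheless names the entire study population for subhypothesis 1 and the specific group for subhypothesis 3, and it defines neither the estimator nor subhypothesis 2.

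*The shifts are assumed.* At 0.3 SD there is almost no inflation. A reader might take 0.8 SD as the plan's own effect, because f2 = .15 converts to d = 2√.15 = 0.77 for two groups. The article gives that value as a minimal detectable effect for a repeated measures analysis of variance, not as an expected shift in a latent slope or a mediator. The fatigue effects in Table 1 run from 0.05 to 0.61, and those are not slope SDs either. This stands in full.

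*One-arm factors are less exposed.* A reader might infer a rate of about 63–65% for activity counts raised by the activity feedback therapy. That requires fatigue to move in that arm alone, with no effect of the mindfulness therapy, against Textbox 1. Under Textbox 1 the figure is about 23%.

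*Step 7 screens the error out.* This is right for factors that reach it. It does not cover the label awarded in Step 6, nor factors not assessed in the control group. The article does not list those. Working alliance is a likely one, since only experimental participants are assigned a therapist. For such a factor the correlation would span the two experimental arms only, so the rates above do not carry over to it.

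**Conclusion.** The point holds as a defect in a written decision rule. As worded, subhypothesis 1 can accept a factor unrelated to fatigue within every arm, and subhypothesis 2 read as equality of correlations barely lowers the rate. The size depends on how far treatment shifts both slopes: negligible at 0.3 SD, about three times nominal at 0.5 SD, and more often than not from 0.8 SD when both arms move the factor.

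A reader might infer that any factor shifted alongside fatigue passes, or that spurious mediators would fill the final Step 7 model. The documents support neither. Small shifts give close to nominal rates, and Step 7 removes nearly all such factors. The exposure is the Step 6 label and the factors that never reach Step 7.

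The figures rest on the assumed shifts, observed slopes, a frequentist test at .05 and independent records. They ignore measurement error in the slopes, Bayesian estimation and former controls contributing twice. The point concerns the mediator objective and leaves the primary efficacy analysis untouched. It should be corrected.

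**What to change.** In Step 6:

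1. State subhypothesis 1 as the common within-arm correlation of Sy and Sz, estimated in a multiple-group growth model with arm-specific means of both slopes, and test that correlation against zero.
2. Define subhypothesis 2 as equality of those within-arm correlations across arms.
3. State what follows if only subhypothesis 2 fails. At present such a factor earns neither label and is not excluded.

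If the authors already intend this model, the change merely records it. No new data or assessments are needed. Step 1 already plans a multiple-group growth model, so the cost is a few sentences.
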